# Evaluation of an antenatal acupuncture intervention as an adjunct therapy for antenatal depression (AcuAnteDep): study protocol for a pragmatic randomised controlled trial

**DOI:** 10.1186/s13063-016-1204-9

**Published:** 2016-02-17

**Keywords:** Acupuncture, Antenatal depression, Intervention, Pragmatic, Protocol, Randomised controlled trial

## Abstract

**Background:**

Depressed pregnant women face difficulty navigating a course between the potentially serious consequences of leaving depression untreated and significant limitations associated with conventional therapies, such as foetal toxicity and teratogenicity. Preliminary evidence is suggestive that acupuncture may provide a safe and effective alternative treatment option for antenatal depression; however, additional research is required. The purpose of this study is to further investigate this treatment possibility, with an additional examination of a potential biomechanistic acupuncture effect.

**Methods/design:**

In this pragmatic randomised controlled trial, we will compare individually tailored, flexible antenatal depression-oriented acupuncture with equivalent attention progressive muscle relaxation and routine antenatal depression hospital care. Eligible women at 24 weeks of gestation with Edinburgh Postnatal Depression Scale scores of 13 or more will be recruited from 2 antenatal clinics in South Western Sydney, Australia. The recruitment goal of 96 is powered to demonstrate a significant difference in Edinburgh Postnatal Depression Scale score severity between acupuncture and usual care, with intervention groups receiving weekly 1-h treatments for 8 weeks from 24 to 31 weeks of gestation. Mental health and quality-of-life assessments will occur at study commencement, intervention weeks 4 and 8 and 6 weeks post-natally via the collection of completed Edinburgh Postnatal Depression Scale scores, Depression, Stress and Anxiety Scale scores and World Health Organisation Quality of Life Scale scores. Adjustment to mothering will also be evaluated at 6 weeks post-natally using the Being a Mother Scale. A putative biomechanistic effect of acupuncture on the oxytocinergic system will additionally be examined by comparing baseline salivary hormone levels with those measured at intervention weeks 4 and 8, as well as leucocyte oxytocin receptor expression at baseline and intervention week 8.

**Discussion:**

Ethical approval was received in February 2015, and recruitment is underway and expected to be completed in July 2016.

**Trial registration:**

Australian New Zealand Clinical Trials Registry ACTRN12615000250538, Registered on 19 March 2015.

**Electronic supplementary material:**

The online version of this article (doi:10.1186/s13063-016-1204-9) contains supplementary material, which is available to authorized users.

## Background

In developed countries, including Australia, depression in pregnancy occurs at rates similar to those seen in non-pregnant women [1, 2], with prevalence reportedly ranging from 7.4 % [3] to 25 % [4] or higher [1] in vulnerable at risk groups [1, 4]. Whilst areas of lower socioeconomic status (SES) have not been identified as a risk factor in all studies [5], they have been shown to contribute to the presence of a greater number of individual psychosocial risks [6] and consequently may result in increased vulnerability. Morbid consequences include a significantly increased risk of obstetric complications [1, 4, 7–11] and post-natal depression in mothers [2, 12], as well as alterations in growth, development [11, 13], autonomic neuroendocrine function [4, 14–16] and mental health [4, 14, 17] in offspring. Treatment recommendations range from psychotherapy or anti-depressants for moderate cases to electroconvulsive therapy or a tricyclic combined with an anti-psychotic for depression with psychosis [18]. Prevailing medical opinion advocates that the consequences of leaving antenatal depression pharmacologically untreated is comparable to or greater than the risks associated with anti-depressant side effects and toxicity [11, 19, 20]. Yet, the efficacy of anti-depressants in pregnancy remains untested in large randomised controlled trials (RCTs), and, whilst expected to be comparable to those observed in non-pregnant populations [21], pregnancy-related pharmacokinetic changes may necessitate a need for increased dosage [20, 22]. Clinicians often reduce prescriptions in an attempt to limit foetal exposure, and resultant levels may therefore be subtherapeutic [22]. Recent evaluations of anti-depressant response rates in non-pregnant populations report modest improvements ranging from 14 % [23] to 32 % overall [24], and more than 50 % of cases failing to achieve remission [25]. Treatment compliance is also an issue, with 45 % partially [26] and 42 % completely discontinuing medication within the first 3 months [27, 28], due in part to unwanted adverse effects [27, 29]. This is especially the case in intentionally conceiving or pregnant women, in whom cessation of medication is particularly common [9, 29], resulting in relapse rates of 68 % compared to 26 % in those who continue medication [30]. Combined pharmacologic treatments and psychotherapies, although considered to be more efficacious, also appear to be limited in regard to depression severity and chronicity [31].

Studies indicate that depressed pregnant women are reluctant to take anti-depressant medication [9, 32] and are significantly more likely to voice a preference for non-pharmacologic options [33, 34]. Preliminary research into acupuncture for the management of antenatal depression, although limited to three clinical studies, appears promising and reflective of similar findings in systematic reviews of acupuncture as a treatment for depression [35–37]. In the first antenatal depression RCT, published in 2004, Manber and co-workers [38] compared 12 sessions of depression-specific, manualised acupuncture with ‘sham’ acupuncture and a massage control in 61 pregnant women with major depression. Significantly higher response rates were reported for depression-specific acupuncture (69 %) compared with massage (32 %) (*p* = 0.031) and a non-significant intermediate response rate in comparison to sham (47 %). The depression-specific acupuncture group also demonstrated a significantly higher average rate of reduction in depression scores within the first month of treatment compared with the massage control (*p* = 0.047). In 2010, Manber et al. [39] conducted a larger RCT of 150 pregnant women and demonstrated significantly decreased symptom severity in the acupuncture group (*p* < 0.05) compared with combined control subjects or sham alone, as well as significantly greater response rates (63.0 %) compared with combined controls (*p* < 0.05) or sham alone (*p* < 0.05). In 2007, Bosco Guerreiro da Silva [40] similarly investigated emotional complaints in pregnancy by quasi-randomising 51 women to a pre-programmed acupuncture protocol with four optional points or a non-treatment control. Symptom severity reportedly reduced by up to 50 % in 15 (60 %) of 25 subjects in the acupuncture group compared with 5 (26 %) of 19 in the control group (*p* = 0.013). In addition, significant reductions in the impact of distress in 3 of 5 life disturbance categories were also reported (*p* < 0.05). Whilst the findings of these three trials appear encouraging, the overall methodological quality is limited by small sample sizes [38, 40], quasi-randomisation and lack of an equivalent attention control [40], unclear randomisation generation and concealment [9, 38], unclear assessor blinding [9, 38, 40], and incomplete baseline and outcome data [9, 38]. Participant and practitioner blinding was performed in the two RCTs [38, 39], as was outcome assessor blinding in one [9, 39]. In all three studies, emotional distress was clinically evaluated.

How acupuncture may reduce depressive symptomology remains uncertain; however, one mechanism by which it may exert an effect is via the oxytocinergic system. This system, regulated by both oxytocin (OT) hormone levels and oxytocin receptor (OTR) activity [41], is responsive to stressors of both physical and psychological origin [42]. The resultant anti-anxiolytic, anti-depressive and stress reducing effects [41, 43] appear to result from adjustments to the hypothalamic–pituitary axis, autonomic nervous system activity [44] and reward centres in the brain [43]. A multitude of physical [42], psychosocial, emotional and behavioural functions [44–48], including mental health and parental-infant bonding [49], have been attributed to this system, and, not surprisingly, disruptions within it are also implicated in a plethora of negative emotional and social phenotypic traits [50]. Studies of the relationship between mental health and the oxytocinergic system are suggestive of dysregulation [51], as lowered [52–60] and elevated OT and OTR levels [51, 61–66], as well as dysregulated patterns of peripheral OT release [66], are seen in participants with depression in a variety of different observational and experimental conditions. The influence of acupuncture upon this system has also been assessed in 12 rodent studies and 1 human study, in which significant positive regulatory effects were reported, directly via radioimmunoassay and/or enzyme-immunoassay or quantitative real-time polymerase chain reaction (qRT-PCR) analysis [67–74], as well as indirectly via assessment of behaviour [75–79]. Further indirect evidence has been provided by 11 human studies examining acupuncture for the preparation, induction or enhancement of labour. Among these studies, significantly reduced requirements for syntocinin augmentation were reported in the acupuncture groups of nine studies [80–88], as was a trend toward less need in the acupuncture group of another [89]. In the remaining study, acupuncture was performed in addition to intravenous syntocinin, and labour effectiveness rates were also significantly improved [90]. Marginal non-significant elevations in syntocinin use were reported in two similar studies [91, 92]; however, methodological issues in both cases may have compromised the results.

As preliminary evidence is suggestive that acupuncture may be beneficial in reducing the severity of antenatal depression and may exert a regulatory effect upon the oxytocinergic system, additional research is warranted to determine whether acupuncture is a viable alternative therapeutic option. The aim of this study is to conduct an RCT to examine the hypotheses that acupuncture, compared with an attention comparator or usual care, reduces the severity and duration of antenatal depression, stress and anxiety; decreases adverse maternal and infant outcomes; improves maternal quality of life and infant bonding; and positively regulates OT and OTR expression.

## Methods/design

### Overview

A pragmatic, parallel-group RCT will be conducted to compare individually tailored, semi-standardised, depression-specific acupuncture with an equivalent attention progressive muscle relaxation (PMR) comparator and usual care. The morbidity of this population is sufficiently serious to maintain existing treatment and evaluate the interventions as adjunctive therapies [93]. The trial design incorporates individualised treatment flexibility [94], typical of a ‘whole systems’ approach [95, 96], within the framework of a semi-standardised protocol [97–100] and is thereby reflective of the recent emphasis on effectiveness studies of acupuncture interventions to maintain ecological validity [101] as well as generalisability and interpretability [98, 99]. The non-specific, placebo-like effects resulting from intervention participation [102, 103] will be estimated via the attention comparator, whereas antenatal depression progression or remission and compliance to standard therapy will be monitored via the non-treatment control [100].

Ethical approval for this study was granted in February 2015 by the Research and Ethics Office of the New South Wales Department of Health, South West Sydney Local Health District (SWSLHD-HREC/14/LPOOL/400) and the Western Sydney University Human Research Ethics Committee (WSU-HREC/H10993). The trial is registered with the Australian New Zealand Clinical Trials Registry (ACTRN12615000250538). The protocol (version 1.0) has been designed in accordance with the SPIRIT (Standard Protocol Items: Recommendations for Interventional Trials) guidelines for interventional trials [104, 105] (see Additional file 1) and will be conducted in accordance with the Declaration of Helsinki (1964) and the International Conference on Harmonization Good Clinical Practice (1996). Any changes that need to be made to the trial protocol will be communicated to all investigators, the ethics committees and the trial registry.

### Eligibility criteria

Women will be eligible if they are at 24 weeks of gestation, ≥18 years of age, have mood disorders and score ≥13 on the Edinburgh Postnatal Depression Scale (EPDS) [106] (indicative of a high probability of current depression) [106, 107]. Women will be excluded if they are experiencing a medically diagnosed major depressive episode ≥2 years in duration and/or have psychotic or manic features rendering them incapable of consent, post-traumatic stress disorder with needle phobia, a current psychiatric assessment of suicidal risk, a condition necessitating bed rest, and/or other major obstetric risks. Participants must also agree not to receive acupuncture or PMR other than that provided within the study.

### Recruitment, setting and informed consent

The study is being conducted at two hospital sites in South Western Sydney, Australia. Both sites provide antenatal outpatient services and are under the governance of the same health authority; however, birthing services are available only in the larger of the two. The region serviced includes suburbs considered to be of disadvantaged SES [108], high ethnic diversity and greater than state average indigenous population density [108, 109]. Pregnant women will be introduced to the study via flyers included in antenatal information packs. Antenatal staff will additionally supply a study poster to all women identified with elevated EPDS scores during routine antenatal screening. Details of these women will be provided to the researcher, who, upon contact, will forward participant information sheets to all interested potential recruits. Once agreeing to join the study, all women will be further screened and, if eligible, randomised after signed informed consent forms containing separate provisions for the collection and use of biological specimens have been obtained in every case (Additional file 2).

### Randomisation and blinding

Participants and practitioners are not blinded to the study; however, data entry and analysis will be blinded. The randomisation schedule was computer-generated to contain three groups of random numbers, enabling stratification for the three different models of antenatal care (obstetrician, standard and caseload midwifery) as well as to randomly contain ‘blocks of three’ within each group, acupuncture, PMR or usual antenatal hospital care (1:1:1). The schedule was generated by the school statistician ([name]) and concealed in opaque envelopes by an independent researcher from the National Institute of Complementary Medicine (NICM) ([name]).

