The principal investigator of this trial ([name]) has 14 years of full-time clinical experience and will conduct all acupuncture sessions, unless unable, in which case a backup acupuncturist with 14 years of part-time clinical experience will be employed. Both practitioners have bachelor’s degrees in acupuncture and are registered with the Chinese Medicine Board of Australia and the Australian Acupuncture and Chinese Medicine Association. The principal investigator will also conduct all PMR sessions, unless unable, in which case a backup associate researcher will be employed.

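### Three is the only block size named for this open three-arm 1:1:1 trial, so about one allocation in three can be deduced by anyone who knows the earlier assignments in the stratum

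*Protocol article*

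**What the plan says.** All references are to the protocol article.

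- **Schedule** (Randomisation and blinding). The list was computer-generated by a statistician, with a separate set of random numbers for each of three models of antenatal care. It was made to "randomly contain ‘blocks of three’ within each group, acupuncture, PMR or usual antenatal hospital care", in the ratio 1:1:1. Site is not named as a stratum.
- **Concealment** (same section). An independent researcher placed the schedule in opaque envelopes.
- **Blinding** (same section). "Participants and practitioners are not blinded to the study; however, data entry and analysis will be blinded".
- **Who delivers treatment** (Interventions, last paragraph). The principal investigator conducts all acupuncture sessions unless unable. The same holds for the comparator: "The principal investigator will also conduct all PMR sessions", again with a backup.
- **Who collects data** (Outcome measures). The principal investigator collects all questionnaires and the saliva specimens.
- **Who recruits** (Recruitment, setting and informed consent). Antenatal staff pass on details of women with raised EPDS scores, and a person described only as the researcher contacts them. Randomisation follows further screening and signed consent.
- **Timing** (Abstract; Trial status). The article appeared on 17 February 2016, with recruitment open and expected to finish in July 2016.

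**The concern.** With three arms at 1:1:1, three is the smallest block possible, and it is the most predictable permuted-block scheme. In an open trial, past assignments become known as women start treatment. An envelope hides the next slip, but it does not stop someone inferring that slip from those already opened in the same block.

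If a person with that knowledge also influences who is approached, how strongly she is encouraged, or how a judgement-based exclusion is applied (for example the catch-all for other major obstetric risks in Eligibility criteria), the arms can come to differ at entry. The primary outcome is a self-reported EPDS score from women who know their arm, so concealment is one of the few protections against bias left in the design. Differences in recorded baseline factors can be adjusted for in part. Selection on unrecorded features such as motivation or expectation cannot.

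**Working it through.** The article gives no predictability figure to reproduce, so the check starts from the stated scheme.

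**Inputs**
- Arms: 3, ratio 1:1:1; block size 3; strata 3 (Randomisation and blinding).
- Planned allocations: 96, or 32 per arm (Sample size).
- Assumed guesser: knows the block size and every earlier assignment in the stratum, and always names the arm with most places left in the block.

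**Blocks of three, exact**
1. First place in a block: three arms remain, so the chance of a correct guess is 1/3.
2. Second place: one arm is used up, so the chance is 1/2.
3. Third place: one arm remains, so the chance is 1.
4. Certain allocations: 1 in 3 = 33.3 %. Over 96 women in complete blocks, 96/3 = 32.
5. Expected correct guesses: (1/3 + 1/2 + 1)/3 = (11/6)/3 = 61.1 %. Over 96 women, 0.611 × 96 ≈ 59.
6. By chance: 1/3 = 33.3 %, or 32 of 96.

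**Incomplete last block.** Stratum sizes are not given. If the three strata were equal, each would hold 96/3 = 32 women, or ten full blocks and two women over. Certain allocations are then 10/32 = 31.3 %. Correct guesses are (10 × 11/6 + 1/3 + 1/2)/32 = 59.9 %.

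**Alternatives.** The fixed sizes were enumerated exactly for complete blocks. The random mixes were simulated: 1,000 runs of 32 allocations, sizes equally likely, with a guesser who knows the set of sizes but not the order in which they occur and updates after each assignment.

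| Scheme | Certain | Best-guess success |
|---|---|---|
| Fixed 3 | 33.3 % | 61.1 % |
| Fixed 6 | 20.0 % | 56.1 % |
| Fixed 9 | 14.3 % | 53.2 % |
| Random 3/6 | 7.8 % | 56.6 % |
| Random 3/6/9 | 3.1 % | 54.3 % |
| Random 6/9 | 4.7 % | 52.9 % |

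The like-for-like baseline for the random mixes is the 32-woman stratum (31.3 % certain, 59.9 % guessed). The conclusion is the same on either baseline. Overall guessing success falls only modestly; the main gain is the fall in certain allocations, by a factor of about 7 (33.3/4.7) to 11 (33.3/3.1).

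**Is the knowledge available?** The principal investigator treats women in both intervention arms and collects questionnaires from all women, so would normally learn assignments in all three arms. That meets the guesser's main condition for at least one member of the team. The block size and the stratification factor were also published while recruitment was open.

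**The case against.** A reader might infer that concealment has failed, or that selection bias has entered the trial. The article does not support that, for these reasons:

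- **Recruiter not identified.** The researcher who contacts women is not said to be the principal investigator. Nor does the article say who confirms eligibility or opens envelopes, and a condensed article may leave that to the full protocol. Knowledge of past assignments is shown; its link to enrolment decisions is not.
- **A single fixed size is inferred.** The wording is loose and could mean that blocks of three were mixed with others. Random order of arms within blocks of three is the more natural reading, and no other size is named. If sizes were in fact mixed, not every third allocation would be certain, and the description would need correcting.
- **Limited room to act.** Entry at 24 weeks of gestation makes it hard to hold a woman back for a later slot, and the EPDS threshold of 13 is objective. Prediction also needs a running tally by care model across two sites.
- **Existing safeguard.** Randomisation already follows eligibility screening and signed consent. This limits late changes of mind, but it does not stop the next arm being inferred before a woman is approached or finally screened.
- **61 % is a ceiling.** It assumes complete knowledge and best play throughout.

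These points limit what can be claimed about bias. They leave the predictability of the scheme as described untouched, and nothing in the article prevents the deduction.

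**Conclusion.** The point holds as a weakness of the stated design. On the natural reading, the last allocation of every block within a care-model stratum is determined by the two before it. For someone who knows the history, about one third of allocations are certain and at most 61 % can be guessed, against 33 % by chance. At least one team member is placed to know that history.

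This rests on three being the only block size used, on blocks being complete or nearly so, and on the guesser having full knowledge of the stratum. It establishes a risk of selection bias whose size in the EPDS comparison cannot be worked out from the article. It should be corrected because the remedy is cheap, but it does not by itself invalidate the trial.

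**What to change.** **If envelopes remain unopened:** have the statistician regenerate the remaining list in each stratum with block sizes varied at random, for example 3/6/9 or 6/9. Do not disclose the sizes to anyone who recruits or treats, and leave them out of public documents until enrolment closes. Keep the planned order of eligibility and signed consent before randomisation. This brings certain allocations to about 3–5 % and best-guess success to about 53–54 %; the sizes named are illustrative.

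**Cost:** new lists and envelopes, plus a protocol change that Overview says must be communicated to all investigators, the ethics committees and the registry. Balance is looser. With a block of nine each arm has three places, so two arms in a stratum can differ by up to three at any moment, against one with blocks of three. How often a stratum would end mid-block cannot be judged, because stratum sizes are not given.

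**If enrolment is complete:** report the block scheme, who knew earlier assignments, who approached women and who opened envelopes, and list predictability as a limitation. The limitations in the Discussion do not currently mention it.
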